### Ethical Considerations

The ethics committee of the APSS approved this study (17241). This study was approved by the ethics committee of the APSS (17241). Recruited women who meet the inclusion criteria and consent to participate will be enrolled in the research. Participants are enrolled voluntarily and do not receive any form of compensation. Their data are pseudonymized using unique codes, and all analyses will be conducted on aggregated data, ensuring that no individual can be identified or traced.

All women who decide to participate in the study will be asked to sign an informed consent form at the time of enrollment after a careful explanation of the project; its aims; how the data will be collected, managed, and processed; the level of involvement required; and the duration of the research, as well as any confidentiality issues. The woman will also be informed of the possibility of quitting the study at any time she wishes without any explanation and that this option would not impact the quality of care or interfere with her course of treatment.

The study will be explained partially by the midwives. In addition, a video recorded by the research team explaining the study, the purpose, and the woman’s involvement in simple, understandable words will also be available. The participants will be informed of the study’s results through the app.

Regarding data protection, a privacy policy will be provided according to articles 13 and 14 of the Regulation EU 2016/679 of the General Data Protection Regulation, explaining the purposes and legal grounds of the data processing, how the personal data will be collected, their categories, how it will be managed, including the data retention period, the obligations of the data controllers, and the rights of the participants who provide data. Personal data are processed for specific research purposes within the scope of public interest tasks of the data controllers. Informed, freely given, voluntary, and explicit consent will be collected regarding the processing of particular categories of personal data (ie, data concerning health and self-reported behavioral habits in the area of lifestyle health). Moreover, specific consent will be requested regarding the possibility of contacting the participant via telephone to conduct the research interviews.

All data collected will be kept confidential and managed by authorized persons. Data necessary for evaluating the study objectives will be pseudoanonymized before processing. Copies of the study information and the privacy policy will be issued to the participant and will always be available in a dedicated section of the app.

The study manager will produce a research report and report the data responsibly and consistently. Personal data will neither be disclosed nor disseminated except in anonymized or aggregated form for publishing purposes. The publication of data from this study will take place independent of the results obtained. The transmission or dissemination of the data, through scientific journals and presentations at congresses, conferences, and seminars, will take place exclusively in anonymous form using only aggregated data that prevents any identification of the participants, even indirectly. This sharing is expected within 1 year after the conclusion of the study.

### Study Outcomes

#### Primary Outcome

The primary outcomes are UX and UE. They will be assessed using 4 questionnaires, namely the User Engagement Scale-Short Form (UES-SF) [34], the System Usability Scale (SUS) [35], the Italian version of the Chatbot Usability Scale (version B; ITA BUS B) [36], and the User Mobile Application Rating Scale (uMARS) [37], which will be administered at different time slots throughout the study, in particular at the end of the week 3 and at the end of the study (ie, week 6).

The end points that will be measured are the scores of the individual items of the questionnaires (UES-SF, SUS, ITA BUS B, and uMARS), the average score of the questionnaires, and the difference between the average score values of the individual questionnaires at different survey times.

UX refers to the overall perceptions and responses that arise from interacting with a product or system, with reference to aspects such as usability, aesthetics, and functionality [38]. UE describes the user’s cognitive, emotional, and behavioral involvement during this interaction [39]. The chosen instruments capture complementary dimensions of UX and UE, including usability, aesthetics, engagement, and satisfaction (for detailed description, refer to Step 3: Participation section). These were selected due to their widespread validation and adaptation in human-computer interaction [40] and their focused use for mobile health app evaluation [41], particularly for chatbot evaluation [36]. Their dimensions are theoretically linked to constructs from cognitive psychology [42] and UX design [43], offering a deep understanding of how users interact emotionally and cognitively with digital products [35,44].

The evaluation of the experience of using the app and the virtual coach (ALBA) and the use of the intervention itself will also be assessed through the semistructured interviews conducted 2 months after childbirth. In this case, qualitative data will be collected to enrich the information related to the primary outcome.

The platform adopted for the intervention allows for recording activity logs, enabling proper mapping of patients’ actions and experiences. This covers a range of logs, assessing whether the patient is appropriately exposed to the intervention protocol while recording use patterns (eg, session execution time, number of accesses, and use patterns of different features). Among the variables considered are any missed sessions or interruptions. These data will be correlated with acceptability scores during the analysis phase. In case a patient does not complete activities and fails to fill in specific questionnaires (leading to data missing), particular pieces of information on patients’ experiences and platform use will be collected during the scheduled postintervention interview sessions.

#### Secondary Outcome

The variable expressing the “psychological well-being” outcome will be assessed by administering 6 self-report questionnaires at the beginning (ie, week 0) and the end (ie, week 6) of the module (refer to Table 1 for a detailed overview of the questionnaire adopted). The end points that will be measured are as follows: a score of the individual items of the questionnaires, the average score of the questionnaires, and the difference between the average score values of the individual questionnaires in the 2 survey times.

**Table 1 table1:** Summary of the questionnaires administered and their timing.

Questionnaires	Screening	At the beginning of the study (week 0)	At the end of week 3	At the end of the study (week 6)	Follow-up (2 months after birth)
K10^a^	✓				
GHQ^b^	✓			✓	
SF36^c^	✓				
PSS^d^		✓		✓	✓
MPFI^e^		✓		✓	
GSE^f^		✓		✓	
ERQ^g^		✓		✓	
COPE-NVI-25^h^		✓		✓	
UES-SF^i^			✓	✓^j^	
SUS^k^			✓	✓^j^	
ITA BUS B^l^			✓	✓^j^	
uMARS^m^				✓^j^	
Qualitative interview					✓

^a^K10: Kessler Psychological Distress Scale.

^b^GHQ: General Health Questionnaire.

^c^SF36: 36-Item Short Form Health Survey.

^d^PSS: Perceived Stress Scale.

^e^MPFI: Multidimensional Psychological Flexibility Inventory.

^f^GSE: General Self-Efficacy Scale.

^g^ERQ: Emotion Regulation Questionnaire.

^h^COPE-NVI-25: Coping Orientation to the Problems Experienced–New Italian Version (25-item).

^i^UES-SF: User Engagement Scale-Short Form.

^j^These usability questionnaires will be administered the following day, so as not to burden the participant during completion.

^k^SUS: System Usability Scale.

^l^ITA BUS B: Italian version of the Chatbot Usability Scale (version B).

^m^uMARS: User Mobile Application Rating Scale.

These psychological instruments were selected for their widespread validation and adaptation in clinical and psychological research, as well as their relevance for assessing various aspects of mental health and coping in the context of digital health interventions. For example, the Kessler Psychological Distress Scale (K10) is a widely used screening tool for psychological distress, with strong validity across cultures, including Italian culture [45,46]. Furthermore, the Multidimensional Psychological Flexibility Inventory (MPFI) and the Perceived Stress Scale (PSS) are highly relevant for examining psychological flexibility and perceived stress, 2 critical constructs for understanding emotional and behavioral responses in mobile health contexts [47-49], (for detailed description of all questionnaires, refer to Step 3: Participation section).

In the framework of this study, these tools are adopted to assess early signals of potential effectiveness of the intervention while assessing UX and UE.

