### Sample Size

This research project is designed as a proof-of-concept study, where a limited sample is sufficient to achieve the intended aims. It was calculated that if nonparametric statistics are conducted (assuming the distribution is not normal), the sample should consist of 24 pregnant women with Bonferroni correction (α=.025). The sample size and power for nonparametric tests (Kruskal-Wallis and Wilcoxon post hoc tests) were calculated according to method reported by Noether [33]. If parametric statistics are conducted (assuming the normal distribution), the sample should consist of 41 pregnant women with Bonferroni correction (α=.025). The sample calculation was further confirmed with the

Power Analysis and Sample Size (NCSS LLC) and Stata (StataCorp LLC) programs, for which the resulting numerosity is 41 participants, assuming null hypothesis (Ho):d=d0, alternative hypothesis (Ha):d≠d0, and considering as study parameters α=.025; mean of group 1 (ma1): 0.000; power: 0.800; mean of group 2 (ma2): 1.000; delta (difference of means, delta): 0.500; expected difference (da): 1.000; and SD of difference (sd_d): 2.000.

Thus, by a power level set at 0.80, a significance level of .025, and considering a 20% potential dropout rate, an estimated 50 pregnant women are needed for recruitment to conduct the study.

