The Coping Orientation to Problems Experienced (COPE) [51] is a shortened version of the COPE Inventory, designed to assess various coping strategies individuals use to deal with stress. This 25-item questionnaire explores strategies, such as active coping, planning, and acceptance, providing a complex picture of an individual’s coping behavior. It uses a Likert scale from 1 (never do it) to 4 (do it often), with a minimum score of 25 points and a maximum of 100. Foà et al [52] translated and validated the questionnaire in Italian, showing good psychometric characteristics.

The Emotion Regulation Questionnaire [53] is a 10-item scale designed to measure the tendency to use 2 emotional regulation strategies as cognitive reappraisal and expressive suppression. Respondents answer each item on a 7-point Likert-type scale ranging from 1 (strongly disagree) to 7 (strongly agree). Balzarotti [54] translated and validated the questionnaire in Italian, showing good psychometric characteristics. In this study, Cronbach α was 0.81 for cognitive reappraisal and 0.84 for expressive suppression.

The GHQ is a self-assessment instrument designed to identify mental health disorders and monitor general psychological well-being. Developed by Goldberg and Blackwell [55], the GHQ is widely used in clinical, research, and public health settings. The 12 items of the questionnaire are formulated to investigate how the individual has been feeling recently, with reference to psychological symptoms (such as anxiety and depression), ability to cope with everyday situations, sleep disturbances, and somatic symptoms. The response is based on a 4-point Likert scale, ranging from “much better than usual” to “much worse than usual” with a maximum score of 36. Fontanesi et al [56] translated and validated the questionnaire in Italian, showing good psychometric characteristics.

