The General Self-Efficacy Scale (GSE) [57] is a psychometric instrument designed to assess an individual’s general perception of self-efficacy, that is, confidence in one’s ability to organize and perform the actions necessary to handle potentially stressful or difficult situations. It consists of 10 statements on which respondents must express their level of agreement on a Likert scale ranging from 1 (not true for me) to 4 (exactly true for me). Items on the scale explore various aspects of self-efficacy, such as problem-solving ability, overcoming obstacles, and handling unexpected situations. The total score, obtained by summing the scores of all items, reflects the individual’s overall perceived level of self-efficacy and can range from 10 to 40. The GSE scale was translated into 28 languages. Scholz et al [58] examined the instrument’s psychometric properties in 25 countries, concluding that the construct of perceived self-efficacy is international and that the GSE is an equivalent measure across different cultures. Cronbach α ranged from 0.79 to 0.90. The Italian adaptation of the GSE scale was developed by Sibilia et al [59].

The K10 is a widely used screening instrument to measure psychological distress. Developed by Kessler et al [45], the K10 is a short questionnaire consisting of 10 items that investigate the frequency of psychological symptoms experienced by the individual in the past month, such as nervousness, sadness, fatigue, and feelings of hopelessness. Each question is scored on a 5-point scale, ranging from “not at all” to “all the time.” Total scores can range from a low of 10 to a high of 50, with higher scores indicating a higher level of psychological distress. The Transcultural Mental Health Center also makes available the validated version of this questionnaire in Italian [46].

The MPFI [47] is an assessment tool that measures psychological flexibility on several dimensions. It investigates how people adapt their thoughts and behaviors in response to changing situations and challenges. The MPFI focuses on various aspects of psychological flexibility, including openness to experiences, present-moment awareness, and value-driven action. The 12 dimensions of flexibility and inflexibility (according to the hexaflex model) are assessed through 60 Likert scale items from 1 to 6. The Italian adaptation of the MPFI scale was developed by Landi et al [48].

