The UES-SF [34] is a short self-report questionnaire to assess UE with a digital solution. This measure includes 12 items based on a 5-point Likert scale, ranging from 1 (strongly disagree) to 5 (strongly agree). The questionnaire consists of 4 factors: (1) focused attention, which indicates the feeling of being immersed in the interaction; (2) perceived usability, which is the negative effect experienced due to the interaction and the effort expended; (3) aesthetic attractiveness, which represents the graphical and visual appeal to a digital solution; and (4) the reinforcement factor (reward). The latter is a single factor that includes duration, which evaluates the overall success of the interaction; novelty, which examines the general interest related to the interaction with a digital solution; and, finally, the perceived engagement factor, which evaluates the overall enjoyment of the interaction. This questionnaire was not available in Italian and was, therefore, translated through the back translation procedure.

The uMARS [65] is a tool for assessing the quality and functionality of mobile apps. It is characterized by a 20-item measure that includes 4 objective quality subscales (engagement, functionality, aesthetics, and information quality) and 1 subjective quality subscale rated on a 5-point Likert scale, ranging from 1 (poor) to 5 (excellent). The total and subscales scores have very high coefficients (0.90 and 0.78-0.80, respectively). The scale has also been validated in the Italian context [66].

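### One average score per questionnaire is a poor endpoint for the MPFI and the ERQ, and the UES-SF average needs a stated direction for its perceived-usability factor

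*Protocol article*

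**What the plan says.** The Secondary Outcome section lists the endpoints for psychological well-being as item scores, then "the average score of the questionnaires, and the difference between the average score values of the individual questionnaires in the 2 survey times", the two times being week 0 and week 6. The Primary Outcome section uses the same construction for its four instruments, with the UES-SF among them: "the average score of the questionnaires, and the difference between the average score values of the individual questionnaires at different survey times". Neither list names a subscale.

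The instrument descriptions under Step 3: Participation show more structure than one average can carry:

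- MPFI: "The 12 dimensions of flexibility and inflexibility (according to the hexaflex model) are assessed through 60 Likert scale items from 1 to 6".
- ERQ: 10 items designed to "measure the tendency to use 2 emotional regulation strategies as cognitive reappraisal and expressive suppression". Reliability is given for each strategy: "Cronbach α was 0.81 for cognitive reappraisal and 0.84 for expressive suppression".
- UES-SF: 12 items scored 1 to 5 in four factors, one of which is "perceived usability, which is the negative effect experienced due to the interaction and the effort expended".

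No reverse scoring is stated for any of the three, and nothing says that reversal is omitted. The Results section then lists feasibility benchmarks. They include significant improvement on the psychological measures, and the measures that section has just named are the MPFI, GSE, COPE and ERQ. Meeting the benchmarks is the condition for moving to a larger trial.

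**The concern.** An endpoint needs a direction before it can show improvement. On the article's own description, the MPFI holds two opposed sets of dimensions, so a rise in its plain average could mean more flexibility, more inflexibility or some of each. The ERQ has a different problem. It holds two strategies that the article treats as separate scales for reliability, but the endpoint list treats them as one quantity.

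The MPFI measures psychological flexibility, which the Secondary Outcome section calls critical, and the intervention is based on acceptance and commitment therapy. If its endpoint cannot be read, the progression benchmark rests partly on a number with no agreed meaning. The UES-SF matters because it is a primary outcome: its average is less informative if one factor runs against the other three.

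**Working it through.** **The plan's own figure.** The Sample Size section uses a paired comparison with expected difference 1.0, SD of difference 2.0, power 0.80 and "a significance level of .025". The standardised difference is 1.0 / 2.0 = 0.5. An exact two-sided paired t calculation gives n = 41 with power 0.805, so the stated 41 reproduces. The point does not depend on this figure; it only sets the scale for the illustration below.

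**Loss in an unreversed average.** Let P items be scored so that higher is better and R items so that higher is worse. If every item improves by D, the raw average changes by

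(P × D − R × D) / (P + R) = D × (P − R) / (P + R).

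The article gives the item totals (60 for the MPFI, 12 for the UES-SF). It does not give the splits, which are assumed here.

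| Scale | Assumed split P/R | Share of D retained |
|---|---|---|
| MPFI | 30/30 | 0/60 = 0% |
| MPFI | 35/25 | 10/60 = 17% |
| UES-SF | 9/3 | 6/12 = 50% |

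The ERQ is left out of the table. The article does not say that either strategy should fall, so no loss can be computed from it.

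**What that would mean for power.** Assume that the two sets of items have mean changes of +1 and −1, each with SD 2, and that their raw changes have correlation ρ between 0 and −0.5. Take n = 41 and two-sided α = .025. With weight w on the positively directed set:

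- Unreversed: mean = w − (1 − w); SD = 2 × √(w² + (1 − w)² + 2w(1 − w)ρ).
- Reversed: mean = 1; SD = 2 × √(w² + (1 − w)² − 2w(1 − w)ρ).

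MPFI, w = 0.5:

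- Unreversed, the mean is 0, so power equals α, 0.025.
- Reversed, the standardised change is 0.707 at ρ = 0 and 0.577 at ρ = −0.5, giving power 0.98 and 0.91.

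UES-SF, w = 0.75:

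- Unreversed, the mean is 0.5 and the standardised change is 0.316 to 0.378, giving power 0.39 to 0.54.
- Reversed, the standardised change is 0.632 to 0.555, giving power 0.95 to 0.88.

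These figures show what hangs on the scoring rule. They do not predict this study's results.

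**ERQ, by comparison of the text.** The instrument description gives two strategies and two reliabilities. The endpoint list gives one average. Reversing items would not settle this, because the average would still combine two different behaviours.

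**The case against.** The strongest objection is that this is scoring detail. Reversal and subscale keys usually sit in the full protocol, the analysis plan or the instrument manuals, and the article nowhere says that raw items are averaged. The average score may mean the mean across women of each questionnaire's properly keyed score; for several other instruments the article gives total-score ranges, not item means. It also shows awareness of subscales by reporting ERQ reliabilities separately. Item scores are endpoints too, so subscales can be rebuilt, and the Secondary Objective section disclaims an efficacy evaluation.

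Much of this stands. A reader might infer that improvement will cancel out; the documents do not support that, because reversal is neither stated nor excluded. Four further inferences also fail:

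- That the UES-SF would cancel. At the assumed 9/3 split a uniform change is diluted by about half.
- That the two ERQ strategies run in opposite directions. The article never says suppression should fall.
- That the COPE total mixes opposed directions. The strategies the article names as examples are not described as opposed.
- That the SUS range of 10 to 50 shows missing reversal. Ten items scored 1 to 5 give that range with or without it.

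The objection does not remove the main point. The endpoint list is explicit, and it offers one score per questionnaire on either reading of average. Where the authors want a subscale they name it, as with the Mental Health scale of the SF-36 at screening. Keeping 60 MPFI item changes in about 41 completers does not replace a defined endpoint.

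**Conclusion.** The stated endpoint is a poor rule for the MPFI and the ERQ. For the MPFI it leaves the direction undefined. If inflexibility items are not reversed, the average keeps 0% of a uniform improvement at a 30/30 split and 17% at 35/25. Full cancellation needs both an even split and equal shifts. For the ERQ the fault is the merging of two strategies; no numerical loss is claimed. For the UES-SF the direction of one factor needs stating, with about half of a uniform change at stake at an assumed 9/3 split. The splits, SDs and correlations are assumptions. The consequence is moderate: the study is exploratory and item scores are kept, but the progression benchmark calls for significant improvement on these same measures. The change should be made.

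**What to change.** In the Secondary Outcome section, replace the single average for two instruments: report MPFI flexibility and MPFI inflexibility as separate composites, and ERQ reappraisal and ERQ suppression as separate scores. For each, state which direction would count as improvement, so that the benchmark in the Results section can be read. In the Primary Outcome section, state that the UES-SF perceived-usability factor is either reversed before averaging or reported separately.

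The cost is a change of wording and scoring code. Two scores become four, so there are two more secondary endpoints, plus one more primary score if the UES-SF factor is reported separately. These can be reported descriptively. No new data are needed, and item-level responses are already collected. The rule should be fixed before outcomes are analysed; the article schedules a preliminary analysis for early October 2025.
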